## Materials

QoL and other outcome assessments are being undertaken using a series of well-validated and reliable measures administered by pen and paper questionnaire. Socio-demographic information is being collected at time of recruitment by interview. Clinical diagnostic and treatment information, including operative time, length of hospital stay, blood loss, time to catheter removal, use of narcotic analgesia and peri-operative complications are being collected through medical record review. Pathology review is being undertaken centrally by our two uropathologists to the trial in conjunction with [name] and includes standardised evaluation of the Gleason scoring using the 2005 ISUP classification, positive margins, extra prostatic capsular extension, neurovascular and seminal vesicle involvement with quality control of selected sections by international pathologists. Prostate-specific antigen testing occurs 2–4 weeks pre-operatively; then at 6 weeks, 3, 6, 9, 12, 18 and 24 months after surgery; and then annually. Biochemical failure (bF) is diagnosed on the first occasion following prostatectomy that the serum PSA is ≥0.2 ng/mL, after which patients undergo total body bone scan and CT scan of abdomen and pelvis for assessment of local and distant failure. Patients are given adjuvant or salvage radiation therapy at the surgeon’s discretion. Clinical staging is being performed using the current UICC TNM staging classification based on the outcome of biopsies, digital rectal exam, transrectal ultrasonography (TRUS), bone scan and contrast-enhanced computerised tomography (CT) pre-operatively. MRI is performed at the surgeon’s discretion. A CT scan of the pelvis and abdomen with 8 mm-slices is performed to evaluate lymph nodes. Pathological staging is being determined from histopathology of the radical prostatectomy specimen along with the findings from lymph nodes with extended lymph node dissection performed for patients with serum PSA >10 ng/ml, primary Gleason ≥4 or cT2b or greater. Postoperative complications are being assessed through chart review supplemented by discussion and letter sent with the patient questionnaire according to the Clavien system of classification.

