**Methods/design:**

200 men per treatment arm (400 men in total) are being recruited after diagnosis and before treatment through a major public hospital outpatient clinic and randomised to 1) Robotic Prostatectomy or 2) Open Prostatectomy. All robotic prostatectomies are being performed by one surgeon and all open prostatectomies are being performed by one other surgeon. Outcomes are being measured pre-operatively and at 6 weeks and 3, 6, 12 and 24 months post-surgery. Oncological outcomes are being related to positive surgical margins, biochemical recurrence +/− the need for further treatment. Non-oncological outcome measures include: pain, physical and mental functioning, fatigue, summary (preference-based utility scores) and domain-specific QoL (urinary incontinence, bowel function and erectile function), cancer specific distress, psychological distress, decision-related distress and time to return to usual activities. Cost modelling of each approach, as well as full economic appraisal, is also being undertaken.

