## Methods/design

### Study aims and hypotheses

The study aims are to assess the quality of life effects of robotic surgery compared with open prostatectomy; determine the economic costs of robotic versus open prostatectomy with regards to both health sector costs and direct and indirect cost to patients; evaluate life expectancy profiles of patients receiving both forms of prostatectomy.

We hypothesise that:

1. There will be no difference between the two groups in terms of surgical and clinical indices of oncological outcome.

2. Patients randomised to robotic prostatectomy will have improved short term (3 months postoperative) quality of life outcomes compared with those randomised to open prostatectomy with regards to pain, physical functioning, fatigue; summary (AQoL-8D and SF36) and domain specific quality of life (urinary incontinence, bowel function and erectile function), time to return to usual activities.

3. Patients randomised to open prostatectomy will have comparable medium (6–12 months) and long term (24 months) quality of life outcomes compared with those randomised to robotic prostatectomy with regards to pain, physical functioning, fatigue; summary (AQoL-8D and SF36) and domain specific quality of life (urinary incontinence, bowel function and erectile function).

4. There will be no difference between the two groups with regards to psychological distress, cancer specific distress and decision-related distress.

5. There will be a short-term and overall cost advantage for open prostatectomy.

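### Discretionary radiation with one surgeon per arm lets prescribing habit alone shift, or mask, differences in biochemical failure and further treatment

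*Protocol article*

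**What the plan says.** Four statements in the protocol article have to be read together.

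- Abstract, Methods/design, on who operates: "All robotic prostatectomies are being performed by one surgeon and all open prostatectomies are being performed by one other surgeon".
- The same section, on outcomes: "Oncological outcomes are being related to positive surgical margins, biochemical recurrence +/− the need for further treatment".
- Materials, on failure: "Biochemical failure (bF) is diagnosed on the first occasion following prostatectomy that the serum PSA is ≥0.2 ng/mL". PSA is measured before surgery and "then at 6 weeks, 3, 6, 9, 12, 18 and 24 months after surgery; and then annually".
- Materials, on postoperative radiation: "Patients are given adjuvant or salvage radiation therapy at the surgeon’s discretion".

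The first hypothesis (H1, Study aims and hypotheses) is: "There will be no difference between the two groups in terms of surgical and clinical indices of oncological outcome". Statistical analyses adds that equivalence procedures will be used where a hypothesis calls for them. Materials also places pathology, including margin status, under central review.

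**The concern.** With one surgeon per arm, the threshold for giving radiation is one person's threshold per arm. Randomisation cannot balance it and a larger sample cannot dilute it. Each surgeon performs only one procedure, so neither can be blind to arm. Two outcomes are exposed.

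1. *Further treatment.* If it is scored from radiation received, it measures the surgeon's threshold as well as the disease.
2. *Biochemical failure.* The rule expressly allows adjuvant as well as salvage radiation. A man irradiated while his PSA is below 0.2 ng/mL may not reach that level, and so counts as failure-free. An identical man who was observed in the other arm may count as a failure.

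This is distinct from surgical skill: two equally skilled surgeons with different radiation habits would still produce it. Because H1 predicts no difference, a bias that hides a difference does as much harm as one that creates it.

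**Working it through.** **The plan's own figure.** The only power statement is for quality of life: 200 per arm, 70% retained (140), d = 0.5, alpha 0.05. Then z = 0.5 × √(140/2) = 4.18, and Φ(4.18 − 1.96) is about 98.7% two-sided, so the claim of more than 90% is correct. It has no bearing on the oncological outcomes, for which the article gives no rates. Everything below is illustration on assumed inputs.

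**Illustration 1: no surgical difference.** Assumptions: a share p of men in each arm (0.25 or 0.40) has adverse pathology. Their 24-month biochemical failure (bF) is 40% if observed and 15% with adjuvant radiation; it is 5% in other men. Every man with bF who has not had adjuvant radiation gets salvage treatment. One surgeon gives adjuvant radiation to u = 10% of adverse cases, the other to 50%.

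- bF = p[0.15u + 0.40(1 − u)] + 0.05(1 − p)
- Further treatment = p[u + 0.40(1 − u)] + 0.05(1 − p)

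| p | Outcome | u = 10% | u = 50% | SE (200/arm) | z | Chance of p<0.05 |
|---|---|---|---|---|---|---|
| 0.25 | bF | 13.1% | 10.6% | 0.0323 | 0.77 | 12% |
| 0.25 | Further treatment | 15.3% | 21.3% | 0.0385 | 1.56 | 34% |
| 0.40 | bF | 18.0% | 14.0% | 0.0366 | 1.09 | 19% |
| 0.40 | Further treatment | 21.4% | 31.0% | 0.0437 | 2.20 | 59% |

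With 140 per arm the chances fall to about 10% and 15% for bF, and to about 26% and 45% for further treatment. The heavier prescriber looks better on bF and worse on further treatment.

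**Illustration 2: other assumptions, still no surgical difference.** High-risk share f = 20–40%; failure 40% in high-risk men without adjuvant radiation and 3% in the rest; adjuvant radiation halves failure; 80% of failures get salvage. One surgeon irradiates a = 10% of high-risk men, the other 30–70%.

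- bF = f[0.40(1 − a) + 0.20a] + 0.03(1 − f)
- Further treatment = f·a + 0.8 × 0.40·f(1 − a) + 0.8 × 0.03(1 − f)
- Smallest further-treatment gap (f = 0.2; a = 0.1 vs 0.3): 9.7% vs 12.4%, or 2.7 points. Largest (f = 0.4; a = 0.1 vs 0.7): 17.0% vs 33.3%, or 16.3 points. The chance of p<0.05 is 14–97% with 200 per arm and 11–89% with 140.
- bF moves the opposite way by 0.8 to 4.8 points. The chance of p<0.05 is 4–27% over both sample sizes.

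**Illustration 3: hiding a true difference.** f = 30%, 3% failure in other men, and high-risk failure of 50% in one arm and 35% in the other. Without adjuvant radiation, bF is 0.3 × 0.50 + 0.7 × 0.03 = 17.1% against 0.3 × 0.35 + 0.021 = 12.6%. If the worse arm's surgeon irradiates 60% of high-risk men, halving their failure, and the other surgeon none, the worse arm becomes 0.3(0.4 × 0.50 + 0.6 × 0.25) + 0.021 = 12.6%. The 4.5-point difference vanishes.

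**What counting early radiation as an event does.** In illustration 1, bF or radiation before bF equals p[u + 0.40(1 − u)] + 0.05(1 − p). That is the further-treatment formula, with the same spurious 15.3% vs 21.3% and 21.4% vs 31.0%. In illustration 3 it gives 0.3(0.6 + 0.4 × 0.50) + 0.021 = 26.1% against 12.6%. The true gap lies between the two versions each time: for p = 0.25, zero lies between 2.5 points one way and 6.0 the other; in illustration 3, 4.5 points lies between 0 and 13.5. Neither version is right alone.

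**Quality of life.** Assume radiation lowers a domain score by 0.5–1.0 SD in treated men. By 24 months, if salvage is radiation with the same effect, the gap in men ever irradiated is 6.0–9.6 points. The arm mean then shifts by 0.03–0.10 SD (0.060 × 0.5 to 0.096 × 1.0).

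**The case against.** The strongest case against is that surgeon discretion is a clinical choice, that nothing in the article contradicts itself here, and that handling of early radiation and the case-report fields belong in the full protocol or SAP. The last part is fair as far as absence goes. But discretion, one surgeon per arm and the PSA-only definition are stated rules, and the distortion follows from applying them.

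Other objections stand and limit the point:

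- The plus/minus sign ties further treatment to recurrence and does not clearly make it a separate endpoint. The article also speaks of need, not receipt. Scoring it from radiation given is a reading, as is taking the discretion to be the operating surgeon's.
- All rates are assumed, including the prescribing gap. Nothing shows that the two surgeons prescribe differently, or how often radiation precedes failure.
- The chance of p<0.05 on a difference test is only a gauge of size, since H1 may be judged by an equivalence procedure.
- That radiation lowers PSA and affects function is general clinical knowledge, not stated in the article.

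A reader might infer that the whole oncological comparison is compromised. It is not: margins are centrally reviewed and later radiation cannot change them. A reader might also infer that salvage radiation masks failure. Failure is fixed at the first qualifying PSA, so only radiation before that point can. And a reader might apply the full 10–16 point gap in adjuvant use (0.40 × p) to quality of life, giving 0.05–0.16 SD. Once salvage in the other arm is counted, that does not hold at 24 months; it could apply only early.

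**Conclusion.** The point holds for biochemical failure and further treatment, not for margins. Prescribing is inseparable from arm, so it can create a difference in these two outcomes or hide one. Under the assumed rates the distortion is larger for further treatment (6.0–9.6 points in the first illustration, 2.7–16.3 in the second) than for biochemical failure (2.5–4.0 and 0.8–4.8 points). The quality-of-life effect, about 0.03–0.10 SD by 24 months, is secondary. The mechanism rests on the stated rules plus the general knowledge that radiation lowers PSA; the size rests wholly on assumptions.

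It is tempting to conclude that H1 should be supported only if failure as defined and the version counting early radiation agree. The working does not support that: the second version carries the further-treatment bias in full, so prescribing habit alone could veto H1.

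**What to change.** Leave clinical management unchanged and protect the analysis.

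- Keep biochemical failure as defined. Add a pre-specified sensitivity analysis in which radiation started before failure counts as an event.
- Report the two together as a bracket, because a difference in prescribing alone pushes them in opposite directions. It is a guide rather than a formal bound. Where they disagree, state that the oncological comparison cannot be separated from surgeon prescribing; neither version should decide H1.
- Record the date, intent (adjuvant or salvage) and PSA at the start of radiation.
- Report further treatment received by arm as surgeon-dependent management and resource use, not as stand-alone evidence on H1.
- Use EPIC and IIEF results that leave out assessments after radiation only as a sensitivity analysis, because the exclusion conditions on a post-randomisation event.

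The cost is a few case-report fields, one extra analysis and a slightly more cautious conclusion on H1. PSA is already scheduled.

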### Self-report measures

#### Anxiety and depression

The Hospital Anxiety and Depression Scale (HADS; [16]) is providing a measure of current psychological distress with subscale scores for anxiety and depression.

### Psychological distress

The Revised Impact of Events Scale (IES-R [17]) is being used to measure men’s cancer specific distress symptoms. The IES-R has three subscales: intrusion, avoidance and hyperarousal. Internal consistencies for the IES-R subscales are good. Epping-Jordan [18] suggest that intrusion and avoidance are more sensitive measures of psychological distress after a cancer diagnosis than generalised distress measures. In men treated for localised prostate cancer intrusion and avoidance have been found to be related to poorer mental health outcomes [19].

### Decision-related distress

For decision-related distress we assess both decisional conflict and decision regret. The Decisional Conflict Scale-Revised (DCS [20,21]) measures a person’s perception of the difficulty involved in making a decision about medical treatments. The revised scale has 19 items covering decisional uncertainty, feeling uninformed, unclear about personal values, and unsupported in decision making, and perceptions of effective decision making. The DCS has been validated in a range of population groups and is sensitive to people making different health decisions, and to the effect of decision aids, with good internal consistency for the total scale. Health decisions assessed with this scale include treatment for localised prostate cancer.

### Domain specific QoL

Domain specific QoL is being measured by the EPIC, the Expanded Prostate Cancer Index Composite [22]: 39 items from this measure will assess functioning in three problem domains: urinary, sexual and bowel. Men are also completing the International Index of Erectile Functioning (IIEF) [23], which allows sexual function to be assessed in five domains: erectile function, orgasmic function, sexual desire, intercourse satisfaction and overall sexual satisfaction. A scale developed by Schover [24] is being used to assess whether men have obtained medical help for sexual dysfunction and the impact of each treatment on their sex life.

### Health related quality of life

Health related quality of life is being assessed with the SF-36 that is the most widely used QOL measure in the world with norms for the Australian general population available. The SF-36 [25] contains a mental health and physical health summary scale suitable to measure the impact of the intervention on patients’ wellbeing. As well, the Assessment of Quality of Life – 8D (AQoL-8D) will be administered [26]. The AQoL-8D is a 35-item scale assessing quality of life on eight dimensions including: independent living, relationships, mental health, self worth, happiness, coping, pain, and sensory perception. The AQoL-8D is the primary outcome instrument for the economic appraisal, has excellent psychometric properties and has been used in over 80 trials in Australia.

### Employment outcomes

Questions are being asked on pre-cancer and current employment status, time off work, returning to work, receipt of sickness and other benefits, unpaid work activities, changes in work role, consequences at work due to cancer, perceived work productivity, assistance from family or others, and carer’s or partner’s work patterns since the participant’s cancer diagnosis.

### Prospective life expectancy modelling

A secondary analysis will identify the comorbidity index which optimises prediction of death from causes other than prostate cancer within 10 years of diagnosis of PCa. We will use the ChI, age-adjusted ChI, ASA, number of comorbid conditions, number of prescription medications (data collected as part of routine history and examination on a proforma) and the TIBI-CaP (an 84 question questionnaire for the patient) as predictor covariates. Time to death from comorbid conditions, as well as from PCa, will be assessed at 5 and 10 years following trial closure. The discriminatory ability of various indices will be assessed using concordance index of the covariate (analogous to area under the ROC curve), with statistical differences between models tested using Integrated Discrimination Index (IDI).

### Economic appraisal

Costs are being assessed from a health sector perspective, covering impacts that fall on ‘government as 3rd party funder’, as well as those affecting patients and their families. Pathway analysis (incorporating decision tree analysis) will be used to clearly identify the activity components for each arm of the trial, complemented by a prospective patient-held cost diary covering the entire trial period (week one to 24 months). The cost categories in the diary are those of travel costs, time costs and productivity costs. Patients fill in the cost diary at one week and then are discharged home with the diary to fill out at home. At each visit patients return the completed cost diary and collect the cost diaries relevant to the next period of the trial.

Costs for each arm of the trial will be analysed by components of the intervention pathway (e.g. pre-consultation, work-up, theatre, post-treatment, follow-up, management/coordination, side-effects, etc.); by expenditure category (e.g. capital, staff, consumables, overheads, other); and by incidence (i.e. who bears the costs). The cost component of the economic appraisal will thus assess the cost drivers from a range of perspectives for both intervention approaches. Downstream costs and potential cost offsets incurred beyond the randomised trial data collection period will be modelled from the literature and expert opinion, with sources clearly documented. Production gains/losses in the general economy will be modelled based on data collections from the trial, using methods developed by Deakin Health Economics [27,28]. Cost-effectiveness results will be reported with and without production effects included.

The economic appraisal will involve a cost effectiveness analysis (CEA), a cost consequences analysis (CSA) and a cost utility analysis (CUA). Outcome measures in the CSA will include incremental changes in the full range of clinical/surgical and psychosocial variables, to paint as comprehensive a picture as possible between resource usage and outcomes. In the CEA outcomes will be reported as incremental cost per outcome ratios (ICERs) for a select range of outcomes that have clinical and/or policy relevance. ICERs will be reported for return to work, the EPIC (the 3 domains urinary, sexual and bowel) and the IIEF (the 5 domains of sexual function). In the CUA, outcomes will be reported as the ‘incremental cost per QALY’ (quality adjusted life year). The AQol-8D will be used as the primary measure of QoL in the economic appraisal, with secondary ICERs developed for the SF-36. Consistency between the QoL results from the AQoL-8D, the SF-36 and the other domain specific QoL measures collected in the trial will be carefully assessed. Standard discounting will be applied to both costs and outcomes, together with detailed sensitivity testing.

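### The return-to-work ICER reported with production effects counts earlier return in both cost and outcome; secondarily, the cost per QALY is likely to be an unstable ratio and needs net benefit beside it

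*Protocol article*

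**What the plan says.** All references are to the protocol article.

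- **Outcomes for the cost-effectiveness ratios** (Economic appraisal): "ICERs will be reported for return to work, the EPIC (the 3 domains urinary, sexual and bowel"), together with the IIEF. That makes nine outcomes: return to work, three EPIC domains and five IIEF domains.
- **Production effects** (same section): "Production gains/losses in the general economy will be modelled based on data collections from the trial", and "Cost-effectiveness results will be reported with and without production effects included". No outcome is exempted.
- **Data on work**: the Employment outcomes section lists "pre-cancer and current employment status, time off work, returning to work" among the items asked. For the patient-held diary, "The cost categories in the diary are those of travel costs, time costs and productivity costs".
- **Cost-utility analysis**: "In the CUA, outcomes will be reported as the ‘incremental cost per QALY’ (quality adjusted life year"), with the AQoL-8D as the main instrument.
- **Expected pattern of effect** (Study aims and hypotheses): hypothesis 2 expects robotic surgery to do better at 3 months, and it names the AQoL-8D and time to usual activities. Hypothesis 3 expects "comparable medium (6–12 months) and long term (24 months) quality of life outcomes". Hypothesis 5 expects open surgery to cost less.
- **Other analyses**: a cost-consequences analysis over the full set of outcomes, discounting, and sensitivity testing.

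**The concern.** Two commitments collide. One makes return to work an effect to be bought. The other values production gained or lost, from trial data, and puts that value into the cost side of every cost-effectiveness result. For the return-to-work ratio, the same event then enters twice: as a saving in the numerator and as the effect in the denominator. A reader of the results would see two cost-effectiveness figures for return to work and might take the lower one as separate evidence for the arm whose patients went back sooner.

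The secondary matter is the cost per QALY. Hypotheses 2 and 3 together put any quality-of-life gain in the first months of a two-year horizon. A gain of that kind contributes little area to the QALY, while the later visits contribute most of the variance. A ratio whose denominator is small relative to its standard error can swing between large positive and large negative values, and a ratio alone is then a poor summary for the value-for-money question that the article sets itself.

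**Working it through.** **The plan's own figure.** The article gives no figure for the economic appraisal. Its only quantitative claim is power (Statistical analyses): 200 per group, 70% retained, d = 0.5, alpha 0.05, over 90% power. With 0.70 × 200 = 140 per group, 0.5 × √(140/2) = 4.18, and Φ(4.18 − 1.96) = 98.7% (two-sided alpha). The claim reproduces as a lower bound and is not in dispute.

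**1. Double count.** Let C be the extra cost apart from production, k the working days gained and w the value placed on a day.

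- Without production effects: C/k.
- With production effects: (C − kw)/k = C/k − w.

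The second ratio is the first less a constant, whatever k is. The documents give no costs or wages, so the inputs below are assumptions (C = 4,000):

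| k (days) | Without | With, w = 200 | With, w = 300 |
|---|---|---|---|
| 5 | 800 | 600 | 500 |
| 10 | 400 | 200 | 100 |
| 20 | 200 | 0 | −100 |

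The shift is −200 or −300 in every row. In the last cell the sign changes only because of the credit for days already counted in the denominator.

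**2. QALY denominator.** Inputs from the article: visits at baseline, 6 weeks, and 3, 6, 12 and 24 months (Abstract, Methods/design); d = 0.5; 140 per arm (70% retained) to 200 per arm (all retained). Assumed, because the article gives none: utility SD 0.15 to 0.25, and equal within-man correlation ρ of 0.5 to 0.7. The article does not tie d = 0.5 to a particular outcome; it is used here because it is the only effect size stated.

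Trapezoid weights in years are 0.058, 0.125, 0.192, 0.375, 0.750 and 0.500 (sum 2.0; sum of squares 1.009).

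- Gain of 0.5 SD at 3 months only: 0.5 × 0.192 = 0.096 SD. Gain at 6 weeks and 3 months: 0.5 × (0.125 + 0.192) = 0.159 SD. Over SD 0.15 to 0.25 the expected difference is 0.014 to 0.040 QALY.
- SD of a man's QALY: SD × √(4ρ + 1.009(1 − ρ)) = 1.583 SD at ρ = 0.5 and 1.762 SD at ρ = 0.7.
- Standard error: that value × √(2/n), giving 0.024 to 0.053.
- Expected z, in which the utility SD cancels: lowest 0.096/(1.762 × √(2/140)) = 0.46; highest 0.159/(1.583 × √(2/200)) = 1.00.
- Chance that the estimated difference has the wrong sign, Φ(−z): 32% at z = 0.46 and 16% at z = 1.00.

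**Effect on the ratio.** In a simulation with a cost difference of 1 unit (SE 0.2) and the effect measured in its own standard errors, the central 95% of ratios ran from −13.7 to 14.3 at z = 0.5 and from −11.2 to 12.0 at z = 0.8. At z = 3 it ran from 0.16 to 0.98.

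**Sensitivity to baseline adjustment.** Adjusting for baseline utility changes the SD multiplier to √(ρS² + (1 − ρ)Q − ρ²S²), where S = 1.942 and Q = 1.006 are the sum and the sum of squares of the post-baseline weights. This is 1.203 at ρ = 0.5 and 1.046 at ρ = 0.7. Then z runs from 0.096/(1.203 × √(2/140)) = 0.67 to 0.159/(1.046 × √(2/200)) = 1.52, and the wrong-sign chance from 25% down to 6%.

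**The case against.** **On the double count.** It touches one outcome of nine, in one of two versions, and the version without production effects is already promised. The article does not say that return to work is measured in days; if it is a proportion back at work, the constant-shift identity does not apply. The valuation method sits in cited work that is not at hand. All of this limits the size of the point. It does not remove it, because nothing exempts the return-to-work ratio and the production effects come from the trial's own data. A reader might also infer that the diary's productivity costs stay in the version without production effects. The text does not say so, and leaving them out is the natural reading; it only needs to be stated.

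**On the QALY ratio.** Planning an ICER where the effect may be small is not an error. Net benefit and acceptability curves are commonly left to a full economic plan, and the article does promise sensitivity testing and a cost-consequences analysis. That stands, and it is why this part is secondary.

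Three stronger readings are not supported:

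- **That the trial expects a QALY difference of about zero.** This takes hypothesis 3 alone. Hypothesis 2 predicts a 3-month gain on the AQoL-8D, which accrues to the QALY, so the expected difference is small and positive.
- **That the EPIC and IIEF ratios divide by zero in the long term.** The article fixes no time point for them. A wrong sign in 50% of trials would follow only for a ratio at a time with no true difference.
- **That the sign is wrong in 34% to 46% of trials.** That needs a 3-month utility gain of only 0.02 to 0.05 with SD 0.15 to 0.25, an effect of d = 0.08 to 0.33 (0.02/0.25 to 0.05/0.15), which is below the article's 0.5.

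**Conclusion.** The double count holds for the return-to-work ICER with production effects, as the two statements are written. It needs no data to establish. Where the outcome is days, its size is exactly the value placed on one day, in favour of the arm that returns sooner. Where the outcome is a proportion, the overlap remains but its size cannot be given from the article. The other eight cost-effectiveness outcomes are not affected by this argument.

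The secondary point holds as a likelihood. At d = 0.5 and without baseline adjustment, the two-year QALY difference is expected to be about 0.5 to 1.0 standard errors, with a wrong-signed denominator in roughly 16% to 32% of trials. Baseline adjustment would improve this to roughly 6% to 25%. These figures rest on assumed correlations and on a gain confined to the first 3 months. The cost-utility question can still be answered from the same data, but the ratio should not carry it alone.

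**What to change.** 1. In the Economic appraisal section, or in the economic plan, state that the return-to-work ICER is reported only without production effects. State also that the diary's productivity costs, and any time costs that value lost work, are left out of its numerator. The other ICERs can keep both versions.
2. Define the return-to-work outcome (days or proportion, and over what period), so that the exclusion can be applied without ambiguity.
3. For the cost-utility analysis, report incremental net benefit over a stated range of willingness-to-pay values, with an acceptability curve, alongside the planned cost per QALY.
4. Do not make the reporting of any ICER depend on whether its outcome difference is statistically significant; that would invite selective reporting.

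The cost is a few sentences of wording and a standard recalculation from data already being collected. Recruitment, visits and questionnaires do not change.
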